### Recruitment, consent, screening and inclusion

2.4

Participants will be recruited through Hersenonderzoek.nl (a Dutch online registry of individuals interested in participating in brain health research), the WUR HNH participant database, local outreach efforts, and (social) media advertisements. Eligible individuals who express interest via email will be invited to attend an in-person information session at WUR. Following this session, interested participants may sign informed consent and subsequently, eligibility will be assessed based on the inclusion and exclusion criteria. Hereafter, participants will undergo the Modified Telephone Interview for Cognitive Status (TICS-m). The TICS-m is used for screening purposes and has been validated for use in older adults, with lower scores indicative of potential MCI or AD (<23) (120, 121). Participants will be given a minimum of one week to consider their participation. Participants will be asked for additional consent for their data as well as any remaining bodily material to be stored up to 15 years and used for other research purposes.

### Sample size calculation

2.5

To date, most fMRI studies investigating gut interventions have focused on emotional processing (122, 123), with few examining working memory (75, 124). To our best knowledge, no studies have evaluated the effects of dietary fibres in older adults with (or without) cognitive impairment or SCD using fMRI-based n-back tasks. Therefore, sample size was calculated based on the effects on memory performance rather than working memory-related BOLD response. However, at the time of designing the study, no study had evaluated the effects of dietary fibres on working memory performance in SCD, which is why our sample size calculations are based on two different study populations (healthy older adults and MCI patients), as the cognitive level of an SCD population could be considered “in between” these two populations. The effect sizes from one dietary fibre (fermented seaweed) (125) and probiotic study (126) were included in the sample size calculation. The included dietary fibre study in healthy older adults demonstrated effects on cognitive function, including working memory (125), while the probiotic study in older adults with MCI showed improvements in immediate memory, visuospatial and delayed memory (126). The Cohen’s f effect sizes were 0.17 and 0.42, respectively, yielding an average effect size of 0.30. Based on this, a total sample size of *n* = 138 was calculated using G*Power (version 3.1.9.7, Universität Kiel, Germany) for an ANCOVA (*α* = 0.05, power = 80%, 4 groups, baseline as covariate). Allowing for an estimated 15% dropout due to fMRI data quality issues and intervention compliance, the final required sample size is *n* = 164 (41 participants per group).

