### Study design and setting

2.2

The PRECODE study is a randomised, double-blinded placebo-controlled, four-armed parallel trial in older adults (60–79 years) with SCD+, with a duration of 26 weeks (Clinical trials identifier NCT06433037). Participants (*n* = 164) will be randomised by block-randomisation (based on sex, age, education and risk factor profile) in four different groups of equal size (*n* = 41). Either one of the following will be administered daily:

Placebo (Maltodextrin) – 7 g per day, divided over two dosages of 3.5 g.Chicory inulin – 12 g per day, divided over two dosages of 6 g.Resistant dextrin – 14 g per day, divided over two dosages of 7 g.Seaweed polysaccharide – 1 g per day, divided over two dosages of 0.5 g. (Seaweed will additionally contain 7 g (3.5 g per dose) of placebo as a volumetric and isocaloric filler.)

Participants will undergo assessments at baseline (*T*_1_), week 13 (*T*_mid_) and at study end (*T*_1_), after 26 weeks at the Division of Human Nutrition & Health (HNH) at Wageningen University (WUR) and the Gelderse Vallei Hospital (ZGV) in the Netherlands (Figure 3). Each participant will have four study visits in total: two at *T*_0_, and two at *T*_1_. In a subselection of participants (*n* = 80), there will be an additional mid-visit (*T*_mid_) in week 13, with five study visits in total. At *T*_0_ and *T*_1_ participants will first visit WUR for investigations and a week later visit ZGV for fMRI scanning. In the week between the visits, participants will collect two faecal samples, wear smartwatches and complete online questionnaires at home. The *T*_mid_ visit consists of a single visit to WUR only. To ensure compliance and to address any questions or concerns that arise during the intervention, five phone calls (10–15 min) will be made to participants during the course of the study.

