#### Statistical methods for primary and secondary outcomes

2.9.1

Data analyses will be performed using R-studio, GraphPad and SPSS. Numerical values will be reported as mean ± SD or confidence intervals. The level of significance is set at 0.05 (two-sided). The Benjamini-Hochberg correction will be used to correct and adjust all *p*-values for multiple comparisons, with the inclusion of a false discovery rate.

The *primary objective* of this study is to investigate the effect of 26 weeks of supplementation with three different dietary fibres (chicory inulin, resistant dextrin, and seaweed polysaccharide) compared to a placebo on working memory (fMRI). Analyses for the primary outcome will compare each fibre group individually to placebo using ANCOVA to adjust for baseline differences, and evaluate the effect of the intervention group at 26 weeks. Specifically, averaged beta weights will be extracted from the regions of interest to determine significant activation at low cognitive load (1-back versus 0-back) and high cognitive load (2-back versus 0-back). *d*-prime values will be calculated to assess working memory task performance. Linear mixed models will be used to evaluate effects on the *secondary and tertiary outcomes* of each dietary fibre individually compared to the placebo at the two different timepoints (baseline and week 26) to measure the interaction group x time. Participants will be set as the random factor, with group and time set as the non-random (fixed) factors. Post-hoc analyses will be performed in case of a significant group x time interaction to understand which fibre(s) specifically differ from the placebo group.

Additionally, *exploratory analyses* will evaluate whether gut- or brain-related biomarkers (e.g., kynurenic acid, serotonin, tryptophan indoles) are associated with cognitive (NTB, MoCA), mood (GDS-15, GAD-7), or physiological outcomes. To elucidate potential mechanisms of the dietary fibre intervention along the MGBA, mediating effects of SCFA levels, TRP metabolite levels and intestinal barrier markers (e.g., LBP, zonulin) between fibre intervention group and cognitive outcomes will be evaluated in case of significant main effects.

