## Initial results

3

By July 2025, baseline measurements were successfully completed. In total, 151 volunteers were randomized into one of four arms and started the intervention. The mean age of our population was 69.4 years (SD = 4.8) and the population consisted of 47.7% females (*n* = 72). The average number of modifiable risk factors was 3.05 (SD = 0.93) and the mean BMI in the population was 27.91 kg/m^2^ (SD = 3.87). Most of the participants (55.6%, *n* = 84) were highly educated, as defined by having at least a 2-year associate degree at a University of Applied Sciences [in Dutch: Hoger Beroeps Onderwijs (HBO)]. Of all subjects, 37.7% carried one or more APOE ε4 allele. The mean MoCA score was 26.09 out of 30 (SD = 2.30) and the average habitual dietary fibre intake was estimated to be 23.68 grams per day (SD = 8.22). Baseline characteristics per intervention arm are presented in Table 6.

**Table 6 tab6:** Baseline characteristics.

		Total	Intervention group			
			A	B	C	D
		*n* = 151	*n* = 37	*n* = 38	*n* = 38	*n* = 38
Sex	% female	47.7	45.9	47.4	50.0	47.4
Education level	% 2-year HBO associate degree or higher	55.6	59.5	44.7	47.4	71.1
APOE genotype	% ε4 carrier	37.7	45.9	39.5	39.5	26.3
Age	mean (sd)	69.4 (4.8)	69.9 (4.7)	69.1 (4.6)	68.5 (4.4)	69.9 (5.6)
Number of risk factors	mean (sd)	3.05 (0.93)	3.03 (0.83)	3.03 (0.85)	3.11 (0.98)	3.03 (1.08)
BMI (kg/m^2^)	mean (sd)	27.91 (3.87)	28.0 (3.88)	28.0 (4.78)	28.2 (3.47)	27.5 (3.30)
Habitual fibre intake (g/day)	mean (sd)	23.68 (8.22)	22.76 (9.29)	23.08 (7.92)	23.91 (6.61)	24.99 (8.94)
MoCA score (max 30)	mean (sd)	26.09 (2.30)	26.16 (2.36)	25.55 (2.81)	26.45 (1.93)	26.18 (2.00)

APOE, Apolipoprotein E; SD, standard deviation; BMI, body mass index; MoCA, Montreal Cognitive Assessment.

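### The stated 138 evaluable participants do not follow from the stated inputs: a four-group ANCOVA at f = 0.30 needs 126, and the error (conservative for the omnibus test) carries into 164

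*Protocol article*

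**What the plan says.** Section 2.5 (Sample size calculation) takes effect sizes from two earlier studies: the "effect sizes were 0.17 and 0.42, respectively, yielding an average effect size of 0.30". The other inputs are alpha 0.05 and "power = 80%, 4 groups, baseline as covariate". From these, "a total sample size of *n* = 138 was calculated using G*Power". The numerator degrees of freedom are not given. The section then inflates this number for an expected loss of 15% and concludes that "the final required sample size is *n* = 164 (41 participants per group").

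Section 2.2 (Study design and setting) repeats the target: "Participants (*n* = 164) will be randomised by block-randomisation". Section 3 (Initial results) reports that baseline measurements were complete by July 2025 and gives the achieved number: "In total, 151 volunteers were randomized into one of four arms and started the intervention". Table 6 shows arms of 37, 38, 38 and 38. Section 2.7.4.3 says that participants who withdraw are not replaced. The article does not restate power for 151.

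Section 2.9.1 describes the primary analysis as an ANCOVA comparing each fibre group individually with placebo.

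**The concern.** The article gives the effect size, alpha, power, number of groups, covariate, software and result, so the result can be checked, and it does not come out. This is not a detail left to a statistical analysis plan. It is a stated result that disagrees with its stated inputs.

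At stake is the yardstick for the trial's size. Both 138 and 164 are presented as what the design needs, and enrolment ended at 151. Without a correction, the achieved sample will be judged against a target that was miscalculated, and the article gives no power for the sample it has.

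**Working it through.** **Inputs.** From section 2.5: f = 0.30 (the unrounded mean is (0.17 + 0.42)/2 = 0.295), alpha = 0.05, power 80%, 4 groups, 1 covariate, 15% loss. From section 3: 151 randomised. Not stated, but fixed by the design: numerator df = 4 − 1 = 3.

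**Method.** Noncentral F power for a fixed-effects ANCOVA:
- noncentrality λ = f² × N
- denominator df = N − 4 − 1 = N − 5
- power = P(F′ > F critical), where F′ is noncentral F with these df and λ
- required N is the smallest with power of at least 0.80.

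**Can 138 be reproduced?** Not with 3 numerator df.

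| f | numerator df | smallest N | power at that N | power at N − 1 |
|---|---|---|---|---|
| 0.30 | 3 | 126 (λ = 0.09 × 126 = 11.34) | 0.803 | 0.799 |
| 0.295 | 3 | 130 (λ = 0.087025 × 130 = 11.31) | 0.802 | 0.799 |
| 0.30 | 4 | **138** (λ = 0.09 × 138 = 12.42) | 0.802 | 0.798 |

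At f = 0.30, numerator df of 1, 2 and 5 give 90, 111 and 149. Using 0, 1, 2, 3 or 5 covariates leaves 126 unchanged at 3 df, so the covariate entry does not explain the gap.

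**Size of the discrepancy.** 138 − 126 = 12 participants (12/126 = 9.5%). With 3 df, 138 evaluable gives power 0.842 at f = 0.30 and 0.829 at f = 0.295.

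**Dropout step.** 138/0.85 = 162.4, so 163, rounded up to 164 for four equal arms. This step is consistent, so 164 inherits the error in 138 and adds none. The same step on the corrected figures gives:
- 126/0.85 = 148.2, so 149 (152 for equal arms)
- 130/0.85 = 152.9, so 153 (156 for equal arms).

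**Achieved enrolment.** 151 × 0.85 = 128.35, about 128 evaluable if the planned loss occurs. Omnibus power at 128 with 3 df is 0.810 at f = 0.30 and 0.7955 at f = 0.295.

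**The case against.** **The error is harmless, because it asks for too many participants.** For the omnibus test this is right, and it limits the weight of the point. It does not make the published figure reproducible. It also leaves little margin: 151 is just above the corrected 149 and just below the 153 that follows from f = 0.295.

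**A planned target and an achieved number may differ without contradiction.** This also stands. Sections 2.2 and 2.5 give the plan, section 3 gives progress, and both are reported openly.

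**A reader might infer that the trial falls 10 short of its requirement (138 − 128) and is therefore underpowered.** The documents do not support this. The 138 is itself wrong, and against the corrected 126 the projected 128 is sufficient at the design effect size. The 128 is also only a projection, since the article reports no attrition or scan-quality losses. From 151 randomised, 138 would remain if losses were 13 (8.6%).

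**A reader might take 4 numerator df as established.** It is not. The article never states the entry. With 3 df, an f of about 0.286 would also give 138, although nothing in the text supports that value. The exact match makes 4 df the likely cause, no more.

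**The gap at f = 0.295 is trivial.** Agreed: 79.5% against 80% is not a material loss of power. It is shown because 0.295 is the actual mean of the two cited values.

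**Conclusion.** The 138 in section 2.5 is wrong as written. The stated inputs require 126 evaluable participants (130 at f = 0.295), and 138 is consistent with numerator df entered as 4 in place of 3. The overstatement is 12 participants at f = 0.30, is conservative for the omnibus test, and passes unchanged in kind into 164.

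The consequence is one of reporting. Assuming the planned 15% loss, the 151 randomised give about 128 evaluable and omnibus power of about 81% at f = 0.30, so the correction favours the trial.

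The assurance covers only the four-group omnibus test at an f of about 0.30. It should not be read as power for the individual fibre-versus-placebo comparisons in section 2.9.1, which this calculation does not address.

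**What to change.** In section 2.5:
- State numerator df = 3 and correct the requirement to 126 evaluable, about 149 randomised at 15% loss (152 for equal arms). If the unrounded f = 0.295 is used, the figures are 130 and 153 (156). If a different numerator df or effect size was intended, state and justify it.
- Keep 164 on record as the original target, with a note that it came from the miscalculated 138. Do not overwrite it with the achieved number.
- Report beside it that 151 were randomised, that about 128 evaluable are projected at the planned loss, and that omnibus power is then about 81% at f = 0.30 (just under 80% at f = 0.295). Update this when actual losses are known.
- Say that these figures are for the four-group omnibus test and not for each fibre against placebo.

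The cost is a text correction. It requires no further enrolment and no change to conduct.

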### Participant timeline and data collection procedures

2.6

All data collection will follow standardised operating procedures with validated tests and standardised tools used for all outcome assessments. The CASTOR electronic data capture (EDC) system (127) will be used for electronic case report forms to minimise data entry errors. Laboratory procedures will be recorded via an electronic journal.

Following confirmation of eligibility and written informed consent, participants will be scheduled for first visits. In preparation, a standardised evening meal, written instructions and questionnaire booklet will delivered to their homes. For all WUR study visits, participants will be instructed to consume the standardised meal the night before their visit and to fast from 22:00 (water and chronic medication permitted).

#### Baseline visits

2.6.1

##### WUR-*T*_0_

2.6.1.1

At the WUR study centre fasting urine and blood (35 mL via venepuncture) will be collected, processed (plasma, serum, and whole blood) and stored at −80 °C. After blood taking, participants will receive a standardised breakfast, followed by a NTB and physiological measurements (Tables 3, 4). During waiting periods, baseline questionnaires on demographic information (age, sex, education, cognitive risk factor profile), medical history, current medication, dietary habits, supplement use, and frailty status will be completed in CASTOR EDC (Table 4). Female participants will also provide obstetric and gynaecological history. Participants will then consume two blue muffins for intestinal transit time (ITT) calculation, receive instructions and materials for home faecal sample collection, gut health questionnaires, and a smartwatch with instructions on mood push notification reporting. The visit will last ~3 h.

**Table 3 tab3:** Overview of biological and physiological outcome assessments.

Outcome assessment marker		Timepoin*t*^1^		
Brain health markers		*T* _0_	*T* _mid_	*T* _1_
(1) fMRI	BOLD signal changes and task accuracy during a 2-back fMRI task	x		x
	*T*_1_/FLAIR anatomical brain scans	x		x
(2) Blood markers	ApoE genotype (total blood)	x		
	Cortisol (serum)	x		x
	Brain Derived Neurotropic Factor (serum)	x	x	x
	Aβ1-42/Aβ1-40 ratio; Neurofilament Light Chain and Glial Fibrillary Acidic Protein levels (plasma)	x		x
	Key kynurenine pathway neurotransmitters and tryptophan metabolites	x	x	x
(3) Urine	Key kynurenine pathway neurotransmitters and tryptophan metabolites	x		x
(4) Smartwatch	Mood via push notifications	x		x
Gut health assessments				
(1) Questionnaires	Bristol Stool Scale	x	x	x
	Gastrointestinal symptom rating scale (GSRS)^2^	x	x	x
(2) Faecal markers	Qualitative microbiota composition (16 s rRNA sequencing)	x	x	x
	Quantitative microbiota (ddPCR)	x	x	x
	Short and branched chain fatty acids	x	x	x
	pH, water content	x	x	x
	Intestinal inflammation (Calprotectin, Lipocalin, β-defensin, sIgA)	x		x
(3) Plasma markers	Intestinal barrier function (Zonulin, iFABP, LBP, sCD14, LPS)	x		x
	Gut hormones	x		x
Metabolic and immune markers				
Plasma/serum	Vitamin D	x		x
	Inflammatory cytokines	x		x
	HbA1c, glucose, insulin	x	x	x
	Lipogram (LDL, HDL, total cholesterol, triglycerides)	x		x
Physiological assessments				
(1) Clinical measurements	Blood pressure, weight, height, BMI	x	x	x
	Grip strength	x	x	x
(2) Smartwatch	Heart rate	x		x
	Physical activity	x		x
Other questionnaires (not outcome measurements)				
(1) Dietary intake	Food Frequency Questionnaire (MIND-diet adjusted)	x	x	x
(2) Participation perception	Study participation perception			x
(3) Compliance diary		x	x	x
(4) General health questionnaires^3^		x		x
(5) Frailty questionnaire (FRAIL-tool)		x		x

^1^*T*_0_: baseline; *T*_mid_: mid-study visit, week 13 (subselection *n* = 80), *T*_1_: end visit, week 26. ^2^ In addition to completion at the three time points, the GSRS will be completed weekly for the first month, to evaluate responses to increased fibre intake. ^3^Population demographics, e.g., age, sex, risk factor profile (LIBRA), medical history, medication, supplement use, for females: information regarding gynaecological and obstetric history. At *T*_1_ a subselection of questions are filled again to determine any changes in health or medication use over the study period. MIND: Mediterranean-DASH diet Intervention for Neurodegenerative Delay.

**Table 4 tab4:** Overview of cognitive assessment questionnaires.

Assessment	Cognitive domains	Completion time	Timepoint^1^			
			S	*T* _0_	*T* _mid_	*T* _1_
Telephonic Interview for Cognitive Status (TICS-m)	Screening tool for cognitive disorders (e.g., MCI, dementia)	30 min	x			
Cognitive Failure Questionnaire	Perception of subjective cognitive decline	10 min		x	x	x
NTB						
Montreal cognitive assessment scale	Testing for light cognitive deterioration and global cognition	15 min		x		
Cognitive functional composite						
ADAS-Cog word recognition	Episodic memory	25–30 min in total		x	x	x
ADAS-Cog orientation	Episodic memory			x	x	x
ADAS-Cog word recall	Episodic memory			x	x	x
Digit symbol substitution test	Executive function			x	x	x
Digit span backward task	Working memory			x	x	x
Category fluency test	Executive function			x	x	x
Mood						
Geriatric depression scale (GDS-15)	Depression	7 min		x	x	x
Generalised anxiety disorder (GAD-7)	Anxiety	10 min		x	x	x

^1^S: Screening; *T*_0_: baseline; *T*_mid_: mid-study visit, week 13 (subselection *n* = 80); *T*_1_: end visit, week 26. ADAS: Alzheimer’s Disease Assessment Scale.

##### Home activities

2.6.1.2

In the week between the WUR and ZGV visits, participants will collect two faecal samples and record blue stool colour appearance for ITT calculation. The smartwatches will be worn from the evening after the WUR visit until the morning of the ZGV visits. Participants will continue the completion of baseline questionnaires in CASTOR EDC, to be finalised before the ZGV visit.

##### ZGV-*T*_0_

2.6.1.3

One week following the WUR visit, participants will visit the ZGV study centre for (f)MRI scanning. Participants will hand in their faecal samples, BSS & GSRS questionnaires and smartwatches. In line with scanning protocols participants will complete a MRI screening form, ensuring MRI-related contraindications have not changed since inclusion eligibility checks. Safety procedures include the provision of MRI suitable clothing and spectacles (if needed, based on visual acuity), earplugs to reduce scanner noise, and placement of foam pads to minimise head movement and enhance comfort. Communication with the participant will be maintained via an intercom and an alarm bell will be provided to alert of any issues during scanning. Prior to scanning, participants will complete a 5-min computerised practice session of the n-back task to ensure task comprehension. After completing the fMRI scan, participants will receive supplements for the 26 week intervention (first 13 weeks, in *T*_mid_ subselection group) and a compliance diary. The visit will last ~1.5 h.

#### Intervention start (week 1)

2.6.2

After the ZGV-*T*_0_ visit, the 26 week intervention starts. Subjects will consume the assigned dietary fibre supplement/placebo during breakfast and dinner. At five occasions, participants will receive a phone call to check compliance, address concerns, and to provide motivation if needed.

#### Mid-study visits (WUR-*T*_mid_)

2.6.3

In week 13, a subselection of participants (*n* = 80) will visit the WUR study centre for the same assessments and procedures as WUR-*T*_0_, except for urine collection. A standardised meal, faecal sample collection materials and blue muffins will be sent to participants’ homes in week 12. The remaining supplements for the next 13 weeks will be provided after the visit. The visit lasts ~3 h.

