##### Cognitive and mood assessments

2.8.1.2

Cognitive and mood outcomes will be assessed *T*_0_, *T*_mid_ and *T*_1_ visits (Table 3). The neuropsychological test battery (NTB) consists of the Cognitive-Functional Composite (CFC) and the Montreal Cognitive Assessment scale (MoCA) - the latter assessed at *T*_0_ only. The CFC battery provides a short and clinically relevant measurement of the cognitive domains that are sensitive to decline in early AD (186). The brief CFC NTB consists of six cognitive tests focusing on episodic memory, working memory and executive functions (186). Components included within the CFC are three components of the Alzheimer’s Disease Assessment Scale-Cognitive subscale (ADAS-Cog) (word recall, orientation, and word recognition), as well as a digit span test, verbal fluency test, and digit symbol substitution test. These tests can detect subtle worse performance in SCD subjects (112). The MoCA scale is a test with high sensitivity and specificity for minor cognitive defects (if scored ≤26/30) (187).

The Geriatric Depression Scale-15-item version (GDS-15) is a concise tool specifically developed to screen for depression in older populations, with established cut-offs and has demonstrated high sensitivity and specificity in older adults (188). The Generalized Anxiety Disorder-7 (GAD-7), a seven-item questionnaire, validated for use in older adults, will be employed to evaluate the presence of anxiety symptoms in daily life (189, 190). Subjective cognitive decline, will be measured via the Cognitive Failure Questionnaire (CFQ), a 25-item scale quantifying the frequency of everyday cognitive lapses (191, 192).

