The inclusion of a mid-study visit after 13 weeks, allows for determining the duration of intervention needed for microbiota and metabolite shifts. Furthermore, mid-study effects on cognition by NTB will allow for insights into timing of onsets of potential protective cognitive effects. Moreover, sex, ApoE genotype and age, influence AD disease stage progression (251). Here, further valuable information on whether these factors may influence the trajectory of potential interventions may be highlighted. Moreover, should there be any significant association evidenced between microbial compositional change and cognitive performance, it might be worthwhile to conduct a follow-up investigation, in which we research if and how long potential microbiota changes last after the trial has been finished, and to compare E4 vs. non-E4 carriers and relatedness of the number of LIBRA risk factors.

Despite its strengths, the study has potential limitations. The self-reported and progressive nature of SCD + may introduce heterogeneity, such as the potential inclusion of individuals with undiagnosed depression and anxiety that may mimic cognitive decline (114, 252). Clinical depression and anxiety are excluded at screening, and will be further assessed by GDS-15 and GAD-7 scores at baseline. Furthermore, some individuals may potentially convert to amnestic MCI over the course of the intervention, which will be evaluated by end-NTB results. Inclusion criteria, such as requirements for general and technological literacy, may additionally introduce bias towards individuals with higher education or better cognitive function. In addition, the inclusion criterion of at least 2 LIBRA risk factors next to presence of SCD may overall limit the generalizability of our findings to SCD individuals with fewer or different combinations of lifestyle risk factors, and should not be generalized to the entire preclinical AD spectrum. Next, long-term fibre supplementation in older adults with increased gastrointestinal sensitivity, may lead to study withdrawal, for which a 15% drop-out rate has been included. Strategies such as dose tapering, morning and evening dosing, and telephone check-ins are used to promote adherence. Furthermore, due to the scope of inclusion and exclusion criteria, including MRI compatibility, extensive recruitment efforts might be needed.

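### About half the sample takes the CFC tests an extra time before week 26, and the stated secondary-outcome model has no term for it: a small, avoidable loss of precision

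*Protocol article*

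**What the plan says.** Section 2.6.3 states that a subselection of 80 "will visit the WUR study centre for the same assessments and procedures as" WUR-T0, apart from urine collection. Section 2.8.1.2 confirms that "Cognitive and mood outcomes will be assessed *T*_0_, *T*_mid_ and *T*_1_ visits", and Table 4 marks each of the six CFC tests at T0, T_mid and T1, with T_mid limited to the subselection. The MoCA is given at T0 only, so the battery repeated in week 13 is the CFC. The CFC is the outcome for the first-listed secondary objective in Table 1.

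Section 2.9.1 sets the secondary-outcome analysis: a linear mixed model comparing each fibre with placebo "at the two different timepoints (baseline and week 26) to measure the interaction group x time", with participant as the random factor and group and time as fixed factors. It goes on to name sex, age and ApoE genotype as potential modifiers, and some baseline characteristics as possible ones. Mid-visit membership is not among them.

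Section 2.6.1.3 shows that membership is known before supplementation starts, because the subselection receives only the first 13 weeks of supply at ZGV-T0.

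**The concern.** Repeating tests such as word recall, symbol substitution and category fluency can raise scores through practice. Every participant has one repeat by week 26, and that shared gain cancels between arms. The 80 have a second repeat, and any further gain from it appears in their T1 score only.

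The participant random intercept cannot absorb this gain, because the intercept is common to T0 and T1. The gain therefore goes into the residual and, to the extent that mid-visit shares differ between arms, into the group x time contrast. What is at stake is precision in the CFC comparison, and a possible later argument over whether a CFC difference partly reflects unequal test exposure.

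**Working it through.** The article gives no figure for a practice effect, so there is no stated number to reproduce.

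**Inputs from the article**
- Mid-visit subset: 80 (section 2.6.3).
- Planned sample: 164, 41 per arm (section 2.2).
- Randomised: 151, in arms of 37, 38, 38 and 38 (section 3, Table 6).

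**Assumptions, not in the article**
- Extra practice gain d from one more sitting: 0.1 to 0.3 SD.
- Residual variance s²: 0.5 to 1 (in units of outcome SD²).
- All 80 places were filled.

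**1. Share with the extra sitting.** p = 80/164 = 48.8% as planned, and 80/151 = 53.0% of those randomised. The product p(1 − p) is 0.250 and 0.249, close to its maximum of 0.25.

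**2. Added variance with equal shares in all arms.** Relative to residual variance, it is d² × p(1 − p) / s².
- d = 0.1, s² = 1: 0.01 × 0.249 / 1 = 0.25%.
- d = 0.3, s² = 1: 0.09 × 0.249 / 1 = 2.2%.
- d = 0.1, s² = 0.75: 0.01 × 0.249 / 0.75 = 0.33%.
- d = 0.3, s² = 0.5: 0.09 × 0.249 / 0.5 = 4.5%.

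The stated model tests change from baseline, so the natural denominator is the variance of change, 2(1 − r), for a baseline to week-26 correlation r. For an assumed r of 0.5 to 0.7 this is 1.0 to 0.6, and the share is 0.25% to 3.7%, inside the range above.

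**3. Power for one fibre against placebo.** Normal approximation, two-sided 0.05, true difference D: power = Φ(D / (s × √(2/n)) − 1.96), with s² multiplied by 1 plus the share from step 2. For D = 0.6 SD:

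| n per arm | residual SD | no extra gain | d = 0.1 | d = 0.3 |
|---|---|---|---|---|
| 41 | 1 | 77.5% | 77.4% | 76.6% |
| 41 | 0.8 | 92.4% | 92.4% | 91.6% |
| 38 | 1 | 74.4% | 74.3% | 73.5% |
| 38 | 0.8 | 90.5% | 90.4% | 89.5% |

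The loss is below 1 point throughout. It depends somewhat on D. With D = 0.4 SD, s² = 0.5, n = 38 and d = 0.3, the standard error is √(0.5 × 2/38) = 0.162 and power goes from Φ(2.466 − 1.96) = 69.3% to Φ(2.466/√1.0448 − 1.96) = 67.4%, a loss of about 2 points.

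**4. Chance imbalance.** If the 80 are a random draw made without regard to arm, the difference in mid-visit share between two arms of 38 has SD √(p(1 − p) × (151/150) × 2/38) = 0.115, and its 95% limit is 1.96 × 0.115 = 22.5 percentage points (21.7 at 41 per arm). The resulting shift in the contrast is d times the difference in share, at most about 0.02 SD (d = 0.1) to 0.07 SD (d = 0.3). The standard error of the contrast is about √(2/38) = 0.23 SD at residual SD 1.

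**The case against.** A reader might infer that the design biases the fibre comparisons, since the article does not say how the 80 were chosen or whether they are balanced by arm. The document does not support that. How a subset is drawn is a detail that a condensed article commonly leaves to the full protocol, and nothing in the text suggests imbalance. Section 2.7.4.1 describes independent, stratified block randomisation with coded groups and identical sachets. If selection is independent of arm, expected bias is zero, and any chance imbalance is already reflected in the standard error. This objection stands.

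A reader might also extend the point to the CFQ, GDS-15 and GAD-7, which are repeated at week 13 too. These are self-report scales, so practice on performance tests is not a mechanism for them. The primary 2-back outcome is not measured at T_mid (Table 3), so it is unaffected. Nor is there any point in advising how to fill mid-visit places, because by July 2025 baseline was complete and all 151 had started.

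The Discussion's statement that "mid-study effects on cognition by NTB will allow for insights into timing of onsets of potential protective cognitive effects" raises a separate question, namely how the week-13 data will be analysed. It confirms that the battery is given then, but it does not bear on the week-26 comparison.

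Finally, the practice gain is assumed, and parallel test versions, if used, could make it smaller. The size is therefore uncertain, and small across the whole assumed range. The objection does not remove the central fact: the article writes out the time points and fixed factors of this model, and a known difference in test exposure affecting about half the sample is not in it. A full analysis plan may add the term.

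**Conclusion.** The point holds as a minor precision improvement to a stated model. At week 26, 80 of 151 to 164 participants are on their third CFC sitting and the rest on their second, and the model as written leaves any resulting gain in the residual. On an assumed gain of 0.1 to 0.3 SD and a residual variance of 0.5 to 1, this is about 0.2% to 4.5% of residual variance. For a 0.6 SD difference at residual SD 0.8 or 1 it costs less than 1 point of power. Chance imbalance could move a contrast by up to about 0.02 to 0.07 SD. No systematic bias is shown, and no conclusion is likely to turn on this. It is worth doing because it is nearly free.

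**What to change.** In the CFC model, add planned T_mid membership and T_mid membership x time as fixed effects. Use planned membership rather than attendance: it is set before supplementation starts, so adjusting for it does not condition on anything that happens under treatment. Report the number of mid-visit participants by arm, which also settles whether the shares were balanced. Record the change before unblinding. The cost is one or two degrees of freedom and one line in the baseline or disposition table; no new data are needed.
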